## Materials and methods

### Methodological design

This is a prospective, exploratory, non-randomized study on adult females (≥18 years old) who will undergo uni- or bilateral mastectomy for clinical indications unrelated to this trial. In this protocol, we broadly define mastectomy as a surgical procedure in which fibroglandular and fatty tissue of the breast is removed. Patients will be recruited at Tampere University Hospital, Finland, the coordinating study center. Multiple study centers in Finland will analyze the resected breast samples.

The multidisciplinary research team (comprising researchers in the fields of surgery, radiology, pathology, oncology, medical physics, computer sciences, and biological sciences) enriches the methodology and scope of this study. The methodology was reviewed by the researchers’ committee and approved by the Ethics Committee of the Wellbeing Services County of Pirkanmaa, Finland (study ID: R230077L), the Finnish Medicines Agency, and subsequently by the institutes participating in this study. The data collection, processing, and analyses are compliant with the European General Data Protection Regulation. Data use and sharing adhere to the data governance policies of the data controller (Tampere University Hospital). The timeline of the study is illustrated in Fig 2. It is worth noting that initial analyses of images and tissue samples will take place as soon as data have been collected from the first 10 resected samples.

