### Participants

Females living in the catchment area of the Wellbeing Services County of Pirkanmaa are eligible for the study if they meet all the inclusion criteria and no exclusion criteria (Table 1). Trial participants will undergo mastectomy/mastectomies based on clinical indications ranging from non-malignancy-related factors (e.g., masculinizing chest reconstruction) to risk-reducing surgery for high-risk mutation carriers and removal of cancer-affected breast(s). This study will not affect the surgical treatment predetermined for the participants as part of their standard of care treatment. Delegated surgeons will identify suitable candidates via interviews and the review of medical records. The surgeon will inform the potential participant about this study and provide a copy of the Participant Information Sheet. Informed consent will be collected prior to any protocol-specific procedure. The participant may withdraw their consent at any point.

**Table 1 pone.0321658.t001:** Inclusion and exclusion criteria.

Inclusion criteria	Exclusion criteria
Aged ≥ 18	Aged < 18
Biological female	Has breast implants
Ability to give informed consent	Inability to give informed consent
Clinical indication for uni- or bilateral mastectomy	

We will recruit a maximum of 100 patients with breast cancer and 100 patients without breast cancer who are due to undergo uni- or bilateral mastectomy. Due to the exploratory nature of this investigation and the fact that insufficient prior knowledge prevents formal statistical calculations, no statistical techniques were used to determine the sample size. To allow the evaluation of the primary and secondary objectives of the study, sample size determination has been primarily based on feasibility and pragmatic considerations of the anticipated recruitment rates. We will include patients with healthy breast tissue, as we are interested in the applicability of our results to screening mammography, which encounters mainly healthy breasts.

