#### Mammographic imaging of the resected breast samples.

Optimal mammographic acquisition parameters are contingent on several factors: the size and density of the breast, along with patient tolerance, determine the compression thickness and force. In addition, the x-ray tube voltage peak (kVp) can be set manually or automatically via the automated exposure control (AEC), of which there are several modes. Milliampere-seconds (mAs) are controlled by the AEC but can also be specified by manual control.

Fig 3 summarizes the study pipeline and data that will be derived from the resected tissue. The resected breast samples will undergo imaging using two mammography devices prior to further procedures. Since imaging parameters are a central variable of our study, each breast sample will be imaged with different combinations of imaging parameters, yielding several images. The acquisition parameters that will be studied are the compressed breast thickness, compression force, kVp, and mAs. We will vary these parameters based on a predefined parameter matrix structured by fixed intervals of kVp and mAs; within each position of this matrix, values of breast thickness and compression force will be used according to the capacity of each specific tissue. For each breast, we will explore a range of parameters covering the clinically used distribution and overlapping with the range of parameters used for all other samples. As there is no available literature on the mammography imaging of *ex vivo* breast tissue, we will use the clinically used compression force as a guideline, but the specific values used for breast compression force and breast thickness will be decided on a breast basis, considering the limitations of each specimen. Other system-specific hardware, such as the target-filter combination and detector, will also be considered for analysis and hence retrieved. Any further information derived from the acquisition process, such as the average glandular dose, will also be retrieved and considered for analysis.

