**Fig 3 pone.0321658.g003:**
[figure not shown]
Study pipeline. Study pipeline and data that will be acquired from the resected breasts. Each resected breast will be scanned with two mammographic imaging machines with several predefined sets of imaging parameters, yielding several images per breast sample in both raw and postprocessed formats. Next, pathological samples will be extracted from the resected breasts for further biological analyses.

The acquired mammograms with their corresponding tags will be stored in digital imaging and communications in medicine (DICOM) format, in FOR PROCESSING (raw) and FOR PRESENTATION (postprocessed) formats. Mammograms will be stored in appropriate storage devices.

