#### Measuring the effect of acquisition parameters on mammographic texture features.

We will evaluate the effect of acquisition parameters on mammograms via the assessment of their texture features, by testing both the sensitivity (in terms of statistically significant differences) and the robustness of texture features in different inter- and intra-machine scenarios. Testing for statistically significant differences between scenarios allows one to determine the magnitude of the impact of the specific parameter under observation; testing for robustness is a complementary approach measuring texture feature sensitivity to imaging parameter variation. We will study radiomic texture features that are common in mammography analysis [49].

We will follow assessment approaches found in the literature on mammography acquisition effects and texture feature robustness assessment [43–46]. The metrics used for differences and robustness assessment will include the correlation coefficient, concordance correlation coefficient, paired differences, variance, means of feature ratios, percentage coefficient variation, and the Kolmogorov–Smirnov test.

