#### Measuring the effect of acquisition parameters at the model level.

Due to rapid technological advances, we are also interested in measuring the effect that the acquisition technique might have on the performance of classical machine learning-based and DL-based models. The first step in this phase of the project is the identification of open-source algorithms published in the field of mammography analysis regarding breast cancer detection. The identified algorithms will be subjected to further development to allow for their use and external validation with our dataset; however, the nature of our dataset allows for the establishment of different validation scenarios beyond using only the images acquired with the clinically optimal acquisition settings. The possibility of testing different “versions” of a dataset acquired from the same breast cohort allows us to study the effect that the acquisition settings can have at the model level.

Furthermore, to the extent that the identified open-source models allow, we will follow the approaches presented in two previous publications that quantified the effect of model robustness to acquisition parameters and vendor using breast phantom mammography data [46] and retrospective mammography data [45]. The first approach (pipeline A) is a two-step scheme: the authors used breast phantom imaging data and self-defined assessment metrics to assess robustness, followed by the evaluation of a breast cancer risk assessment model by using groups of features with different levels of robustness. The statistical significance of the different performances obtained was assessed via a linear mixed-effects model. The second approach (pipeline B) used retrospective screening mammograms obtained with two different mammography machines. Each subject had been previously imaged with both vendors in different screening rounds. Texture feature robustness was assessed via statistics describing equivalence, correlation, and sample distributions, and the redundancy of features was identified via clustering. To assess the effect of robustness and redundancy on the performance of a robustness assessment model, an inter-vendor scheme was constructed by training the model using one of the vendors as a reference sample and testing it on the images of the other vendor.

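### The two-sample Kolmogorov–Smirnov p-value assumes independent samples, but every imaging scenario uses the same breasts, so the test is too conservative to support calling a feature robust

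*Protocol article*

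**What the plan says.** The section of the protocol article on measuring the effect of acquisition parameters on texture features says that features will be compared between settings within a machine and between machines, both for statistical significance and for robustness. One list of metrics serves both purposes. It opens with the correlation and concordance correlation coefficients and continues with "paired differences, variance, means of feature ratios, percentage coefficient variation, and the Kolmogorov–Smirnov test". No paired or permutation form of the last test is named.

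The design puts the same breasts in every scenario:

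- The Fig 3 legend: "Each resected breast will be scanned with two mammographic imaging machines with several predefined sets of imaging parameters".
- The section on mammographic imaging of the resected samples: "each breast sample will be imaged with different combinations of imaging parameters, yielding several images".
- The section on the model level presents this as an advantage: "The possibility of testing different “versions” of a dataset acquired from the same breast cohort".

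On numbers, the Participants section states: "We will recruit a maximum of 100 patients with breast cancer and 100 patients without breast cancer". It adds that "no statistical techniques were used to determine the sample size". A woman may contribute one or two breasts, since participants are those "who will undergo uni- or bilateral mastectomy for clinical indications unrelated to this trial".

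**The concern.** The reference distribution of the two-sample Kolmogorov–Smirnov test is derived for two independent samples. Here each value in one scenario has a partner from the same breast in the other. If a breast with a high feature value under one setting also tends to have a high value under another, the two empirical distributions move together. The gap between them then varies less than the test assumes, so the test rejects too rarely.

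The study exists to find out whether acquisition produces a measurable batch effect. A test that rejects too rarely errs towards finding none, and a non-significant result invites the label of a robust feature. Re-imaging the same tissue is the main strength of the ex vivo design, and this test makes no use of it.

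**Working it through.** **Inputs.** From the article: at most 100 + 100 = 200 women, and the same breasts in each scenario. Not given, so assumed: nominal two-sided level 0.05, one breast per woman, one image per breast per scenario, normally distributed features, within-breast correlation r of 0.5 to 0.9, and a true shift of 0.2 SD. The article states no power or level, so there is no planned figure to reproduce.

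**Step 1: why the size falls.** At the median, the variance of the gap between the two empirical distribution functions, relative to its value under independence, is 1 − (2/π)·arcsin(r).

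- r = 0.5: 1 − 0.333 = 0.667, so the SD is √0.667 = 0.82 of what the test assumes.
- r = 0.8: 1 − 0.590 = 0.410, SD ratio 0.64.
- r = 0.9: 1 − 0.713 = 0.287, SD ratio 0.54.

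**Step 2: why power falls as pairing gets stronger.** With 200 values per scenario, the 5% critical gap is 1.358·√(2/200) = 0.136. A 0.2 SD shift gives a largest true gap of 2Φ(0.1) − 1 = 0.080, which is below that threshold. The test rejects only when noise carries the observed gap past 0.136, and a higher r leaves less noise.

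**Step 3: the paired comparison.** The difference has SD √(2(1 − r)), so power is about Φ(0.2·√200 / √(2(1 − r)) − 1.96).

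- r = 0.5: Φ(2.83 − 1.96) = 0.81.
- r = 0.8: Φ(4.47 − 1.96) = 0.99.
- r = 0.9: Φ(6.32 − 1.96) = 1.00.

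**Step 4: simulation** (4,000 datasets per row, asymptotic Kolmogorov–Smirnov p-value, paired t test).

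| r | KS size | KS power | Paired size | Paired power |
|---|---|---|---|---|
| 0 | 0.048 | 0.40 | 0.042 | 0.49 |
| 0.5 | 0.013 | 0.38 | 0.057 | 0.81 |
| 0.8 | 0.001 | 0.31 | 0.051 | 0.99 |
| 0.9 | 0.000 | 0.24 | 0.057 | 1.00 |

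The exact p-value gives lower power still: 0.31 at r = 0.5 and 0.17 at r = 0.9. At r = 0 the test holds its size, so the loss comes from the pairing.

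**Step 5: the remedy.** Permuting scenario labels within breast restores the size to about 0.05. Power for the same shift is then about 0.6 at r = 0.5 and above 0.95 at r = 0.9.

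**Step 6: why the woman should be the unit in the remedy.** If 25% of women contribute two breasts and these are counted as independent, a paired test at nominal 0.05 has size 0.06, 0.08 or 0.10 when the differences correlate within a woman at 0.3, 0.6 or 0.9. The bilateral share and these correlations are assumptions. They support the choice of unit and are not a finding about the plan.

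**The case against.** The strongest reply is that the Kolmogorov–Smirnov test is one of seven listed metrics, that the list is open-ended, and that nothing says this test alone decides whether a feature is robust. Paired differences, the efficient comparison, are already in the plan. The test may be meant only to describe distributions, as in the source study for pipeline B. The study is exploratory and fixes no significance level. All of this stands, and it limits the harm to conclusions that rest on this test. It does not remove the mismatch: the article announces significance testing, names this test among the means, and gives no form of it that suits same-breast data.

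A reader might infer three stronger criticisms, which the article does not support.

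- *That the other listed metrics also assume independent images.* Paired differences need independence between pairs, not between images. Concordance, correlation and feature ratios match image to image. The descriptive measures have no error rate until a test or interval is attached.
- *That error rates are wrong in both directions.* Inflation would need images or breasts to be pooled as if independent, for example in a comparison of women with and without cancer. The article states no such feature test and does not say that images or breasts are treated as independent. Handling of two breasts per woman is commonly left to the full protocol or analysis plan.
- *That a particular mixed model must be the main analysis.* The form of the batch-effect model is likewise such a detail, and pipelines A and B are adopted as guidelines at the feature level too.

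**Conclusion.** The point holds in a narrow form: the standard Kolmogorov–Smirnov p-value is the wrong reference for scenarios built from the same breasts. The direction, too few rejections, follows from the stated design once features correlate positively within a breast. The size depends on the assumptions listed above. Over correlations of 0.5 to 0.9, the size is about 0.01 to 0.00 instead of 0.05, and the power for a 0.2 SD shift is roughly 0.2 to 0.4 instead of 0.8 to 1.0. The consequence is missed batch effects where this test decides, not across the whole feature analysis. It is worth correcting, but it is not critical to an exploratory study that already lists paired differences.

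**What to change.** In the feature-level section, state one of two uses for the Kolmogorov–Smirnov statistic: a descriptive distance without a p-value, or a test whose p-value comes from permuting scenario labels within breast, with both breasts of a woman permuted together. Where a scenario holds several images per breast, they should move as a block. Base significance statements on the paired differences already listed, with the woman as the resampling unit, and say that a non-significant Kolmogorov–Smirnov result will not by itself classify a feature as robust.

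The cost is a few sentences of analysis wording and a little more computation. No new images, participants or tissue are needed.

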#### Measuring the effect of acquisition parameters at the model level.

Due to rapid technological advances, we are also interested in measuring the effect that the acquisition technique might have on the performance of classical machine learning-based and DL-based models. The first step in this phase of the project is the identification of open-source algorithms published in the field of mammography analysis regarding breast cancer detection. The identified algorithms will be subjected to further development to allow for their use and external validation with our dataset; however, the nature of our dataset allows for the establishment of different validation scenarios beyond using only the images acquired with the clinically optimal acquisition settings. The possibility of testing different “versions” of a dataset acquired from the same breast cohort allows us to study the effect that the acquisition settings can have at the model level.

Furthermore, to the extent that the identified open-source models allow, we will follow the approaches presented in two previous publications that quantified the effect of model robustness to acquisition parameters and vendor using breast phantom mammography data [46] and retrospective mammography data [45]. The first approach (pipeline A) is a two-step scheme: the authors used breast phantom imaging data and self-defined assessment metrics to assess robustness, followed by the evaluation of a breast cancer risk assessment model by using groups of features with different levels of robustness. The statistical significance of the different performances obtained was assessed via a linear mixed-effects model. The second approach (pipeline B) used retrospective screening mammograms obtained with two different mammography machines. Each subject had been previously imaged with both vendors in different screening rounds. Texture feature robustness was assessed via statistics describing equivalence, correlation, and sample distributions, and the redundancy of features was identified via clustering. To assess the effect of robustness and redundancy on the performance of a robustness assessment model, an inter-vendor scheme was constructed by training the model using one of the vendors as a reference sample and testing it on the images of the other vendor.

Pipelines A and B will be used as guidelines to assess acquisition effects at both the texture feature and the model level. The main adjustments will be the use of *ex vivo* tissue instead of a breast phantom in the case of the first study and testing intra-acquisition settings scenarios in addition to intra-machine in the case of the second study.

#### Biological and histopathological analysis.

Biological, histopathological, and genetic analyses and imaging studies will be conducted on the tissue samples to determine their structural, biological, histopathological, and genetic features to study how biological factors across different scales correlate with mammographic texture features. The tissue analyses will include, for example, routine hematoxylin-eosin staining for tissue morphology, label-free second harmonic generation imaging or Masson trichrome staining for collagen in fibroglandular tissue, cytokeratin staining for glandular epithelium, and fluorescent lipid staining for adipocytes. Tissue stainings will be analyzed using microscopic and/or mesoscopic imaging combined with modern digital pathology methods, including AI-driven image analysis.

### Ethics and dissemination

We sought a favorable opinion from the Ethics Committee of the Wellbeing Services County of Pirkanmaa (study ID: R23077L) and an organizational permission to conduct the study. The data will be pseudonymized at source. This study does not affect the clinical treatment of the participants. There will be no safety reporting on this study, since the procedures will be conducted on resected breast tissue; hence, the study does not represent risks for humans.

The study results will be published in peer-reviewed scientific journals, conference proceedings, or as part of science communication. Data use and sharing adhere to the data governance policies of the data controller (Tampere University Hospital, Finland).

## Discussion

This study aims to test whether mammography imaging acquisition introduces a batch effect and its potential impact in computerized analysis. To achieve our goals, this study will use mammography images derived from resected breast tissue, which raises questions about the imaging procedure. The relative forces experienced by the components of an *ex vivo* sample differ from those of *in vivo* tissue due to the lack of attachment to the pectoralis wall in the *ex vivo* scenario. The behavior of the resected tissue during breast compression is unpredictable, as there is no available information about this procedure. We anticipate that this will limit the number of breast compression forces and thicknesses that we will be able to use and achieve during imaging. Furthermore, the discrepancies in tissue properties that pertain to the interaction of *in vivo* and *ex vivo* breast tissue with x-rays have not been studied. At the analysis level, AI-based mammographic approaches found in the literature have been designed for images acquired from *in vivo* breasts. The extent to which the use of resected breasts will restrict the direct translation of our results to an *in vivo* scenario is impossible to predict. We will assess the differences in mammograms acquired from *ex vivo* tissue at both the quantitative level, comparing their mammographic features with those of *in vivo*, retrospective counterparts (retrieved from open-source repositories), and at the qualitative level, via radiologists’ visual assessment of their likeness to an *in vivo*-acquired mammogram. Furthermore, this study will enable determination of the critical features for mammograms, the relevance of which for *in vivo* mammography settings can further be tested in prospective patient studies.

The results of this study will shed light on one of the main factors responsible for the lack of generalizability of AI-based models. Knowing the extent and ways in which acquisition parameters affect the mammographic image at the quantitative level, and ultimately the AI models based on them, will guide future approaches in addressing the batch effect as a composite problem, instead of a homogeneous issue.

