### Artificial intelligence and the current understanding of the factors affecting its performance

Although AI-based mammography analysis has demonstrated great potential, the lack of access to representative datasets [31–34] and model degradation due to data distribution shift [35–39] are commonly reported challenges that are hindering the translation of AI to clinical practice. The high heterogeneity between mammography datasets due to imaging parameters is a recognized challenge for the development of robust computerized analysis tools. Research to understand the effect of these sources of heterogeneity for the goal of computerized assessment is still lacking [35,40,41].

The effect of non-biological sources of heterogeneity—imaging acquisition and the manufacturer’s pre- and post-processing—is referred to as the *batch effect*. The batch effect has been shown to introduce changes in computerized image features, which also affect their robustness and reproducibility [42–44]. This in turn is reflected in the performance of breast cancer risk assessment [37,45,46] and breast cancer classification [35] models. On the other hand, the biological properties of the breast, through the interaction with the x-ray radiation, create the radiomic features; the heterogeneity that arises from them is, technically, desired. However, as radiomic biomarkers are not initially derived from biological samples but rather from radiological images, the effect of the interplay between image acquisition and the underlying biology on the performance of AI-based radiomics is unknown [24]. Research into the role of fibroglandular and adipose tissue—from the genetic and molecular levels to cellular and tissue levels—on radiomic features is currently scarce, but it is needed to explain how radiomic features may predict the future development of cancer.

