Although the amount of existing clinical mammography data is large, the retrieval of an appropriate dataset to study the sources of heterogeneity mentioned above is infeasible from existing, accessible repositories. As a source of ionizing radiation, mammographic imaging limits the number of times a person can be imaged. As a result, the acquisition parameters in clinical practice used to capture each specific mammogram are optimized for image quality and for as low a radiation dose as is reasonably achievable: this limits the range of acquisition parameters that are employed on the different breasts, which, in turn, limits the possibilities of analyzing the effect of acquisition parameters on computerized analysis of mammograms derived from *in vivo* breasts. A dataset for the study of the sources of heterogeneity would require reimaging of the breast with different acquisition settings. Moreover, the analysis of biological factors requires the collection of tissue samples. Breast tissue is not normally resected unless there is a suspicion of cancer. Previous studies have used phantoms and retrospectively collected mammograms [42,44,45], which can only partially address the association between acquisition parameters and textural features and do not allow for the systematic evaluation of the effect of biological factors on radiomic features.

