#### Breast cancer risk survey.

The trial participants will complete a questionnaire on their background information regarding comorbidities and cancer risk. The researchers will collect register-based clinical data from the healthcare records. These data will be used to determine individuals’ breast cancer risk scores within 5 and 10 years using the Gail model [47] and the Tyrer–Cuzick risk calculator [48], respectively.

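### The ex vivo versus in vivo comparison uses repository images of other women, so it cannot isolate the ex vivo effect from device, processing, settings and case mix

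*Protocol article*

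**What the plan says.** The Discussion of the protocol article accepts that the limits on carrying specimen results over to living patients cannot be foreseen. It plans two checks. The quantitative one compares specimen features with those of in vivo "retrospective counterparts (retrieved from open-source repositories". The qualitative one works "via radiologists’ visual assessment of their likeness to an" in vivo mammogram. No other in-study evidence on this question is described; relevance in vivo is referred to later patient studies.

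Three other places bear on the choice of comparator:

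- The Introduction section on factors affecting AI performance says: "The high heterogeneity between mammography datasets due to imaging parameters is a recognized challenge". It defines the batch effect to include processing: "The effect of non-biological sources of heterogeneity—imaging acquisition and the manufacturer’s pre- and post-processing—is referred to as the" batch effect.
- The same section says that retrieving a dataset fit to study these sources "is infeasible from existing, accessible repositories".
- The section on mammographic imaging of the specimens says: "The resected breast samples will undergo imaging using two mammography devices prior to further procedures". It adds that settings will span those used in the clinic.

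The Participants section describes the case mix: women having mastectomy for cancer, for risk reduction or for non-malignant reasons, at most 100 with and 100 without breast cancer.

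**The concern.** Every ex vivo image comes from one group of women on two devices. Every in vivo image comes from different women in outside datasets. Ex vivo status and dataset therefore change together. The protocol's premise is that datasets differ in their features because of acquisition and processing, so a specimen-versus-repository difference has at least three candidate explanations: the ex vivo state, the batch, and the population. A finding of no difference is no safer, because shifts in opposite directions can cancel.

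At stake is the quantitative evidence on whether ex vivo images behave like in vivo ones. The Participants section states an interest in screening mammography, so readers will look to this comparison for reassurance that it cannot give.

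**Working it through.** The plan states no effect size, SD, alpha or power for this comparison, and the sample size was not statistically derived. There is no figure to reproduce. The question is whether the ex vivo effect can be identified.

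**Estimability.** Take a linear model for one feature with an intercept, an ex vivo indicator, an indicator for the second study device, and indicators for the source of the in vivo images. Each row below is one kind of image.

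1. *Repositories A and B on other devices* (the plan's comparison). Columns: intercept, ex vivo, device 2, A, B. Rows: (1,1,0,0,0), (1,1,1,0,0), (1,0,0,1,0), (1,0,0,0,1). The ex vivo column equals intercept − A − B. Rank 4 of 5; ex vivo effect not estimable.
2. *Repository on a study device model, other women.* Columns: intercept, ex vivo, device 2, study cohort. Rows: (1,1,0,1), (1,1,1,1), (1,0,0,0). The ex vivo and cohort columns are identical. Rank 3 of 4; not estimable. Matching on device does not rescue the comparison.
3. *Participant's own preoperative image on a study device.* Columns: intercept, ex vivo, device 2. Rows: (1,1,0), (1,1,1), (1,0,0). Rank 3 of 3; estimable.
4. *Participant's own preoperative image on another device.* Columns: intercept, ex vivo, device 2, other device. Rows: (1,1,0,0), (1,1,1,0), (1,0,0,1). The ex vivo column equals intercept − other device. Rank 3 of 4; not estimable. Differences between women are removed but the device shift stays.

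**Illustrative size.** These values are assumptions: one image per subject, 200 specimen and 200 repository images, two-sided alpha 0.05, shifts in SD units. The standard error of the difference is √(2/200) = 0.10 SD. With no true ex vivo effect, the probability of a significant result is about Φ(shift/0.10 − 1.96):

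- batch shift 0.25 SD: Φ(2.50 − 1.96) = Φ(0.54) ≈ 0.70
- batch shift 0.50 SD: Φ(5.00 − 1.96) = Φ(3.04) ≈ 0.999

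More images shrink the 0.10 but leave the shift in place.

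Now let the true ex vivo effect be 0.5 SD. The expected contrasts are:

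| Comparator | Batch shift 0.25 SD | Batch shift 1.0 SD |
|---|---|---|
| Repository | 0.5 + 0.25 = 0.75 | 0.5 + 1.0 = 1.5 |
| Own image, other device | 0.75 | 1.5 |
| Own image, study device | 0.5 | 0.5 |

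With a batch shift of −0.5 SD the repository contrast would be 0.5 − 0.5 = 0, and a real ex vivo effect would be hidden.

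**The case against.** The strongest reply is that this is one sentence in the Discussion of an exploratory study that is candid about the limits of translation. The main objective compares settings within the same specimen and does not use repository images. That stands, and it confines the point to the translation check.

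A second reply is that matching or adjustment may be specified in a full protocol or analysis plan not shown here. Settings could indeed be matched, since the specimen settings span clinical use and the DICOM tags are kept. But the comparator itself is stated, and case 2 shows that the cohort difference survives matching on device.

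A third reply concerns the remedy, and much of it stands. The documents do not say that preoperative mammograms exist or on which device they were taken. Mastectomy is defined broadly, so a specimen need not be the whole imaged breast. Specimen compression is described as unpredictable, so thickness and force may not match closely.

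Some stronger readings are tempting but unsupported:

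- *A reader might infer that participants' own mammograms would in any case separate the ex vivo effect from the batch effect.* Case 4 shows that they do not when taken on another device.
- *A reader might infer that the paired comparison settles transfer.* It does not. An in vivo image is taken at clinically chosen settings, and the Introduction notes that radiation limits repeat imaging. The pair gives an offset in feature level, not the in vivo effect of changing kVp or mAs.
- *A reader might infer a fixed gain in precision from pairing.* None can be quoted, because it depends on the same-breast correlation and on the numbers of usable pairs and repository images, none of which is given.
- *A reader might take "The researchers will collect register-based clinical data from the healthcare records" to mean that archived images are already available.* That section concerns data for risk scores and does not show access to images.
- *A reader might fault the radiologists' rating as unblinded.* The article does not describe the reading set-up, and such detail is commonly left to fuller documents.

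**Conclusion.** The point holds for the translation check only. As stated, the repository comparison cannot isolate the ex vivo effect, whether it shows a difference or a similarity. This follows from the structure of the comparison and from the protocol's own account of heterogeneity between datasets; it does not depend on sample size. The size of the bias is unknown. The probabilities of 0.70 and 0.999 rest on assumed shifts and assumed numbers, and show only that a modest shift would be enough to mislead.

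Participants' own preoperative mammograms improve matters, but isolate the ex vivo effect only on a study device, with the same processing and closely matched settings. It is worth changing because the improvement is cheap, but nothing in the within-specimen analyses of acquisition settings is put in doubt.

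**What to change.** - Where consent and permits allow, retrieve participants' existing preoperative mammograms of the resected breast with their DICOM tags.
- Make the main ex vivo versus in vivo comparison a paired one. Restrict it to preoperative images from one of the two study devices with the same processing, and pair each with the specimen image from that device closest in kVp, mAs, thickness and force.
- Report the repository comparison, and any pairs from other devices, as descriptive only.
- State that the paired result estimates a level offset in features and does not show whether acquisition-setting effects transfer in vivo.
- If no same-device images can be obtained, state that the ex vivo effect cannot be isolated.

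The cost is archive retrieval and a check that consent and permits cover it; no new exposure or extra reader is needed. The downside is a subset analysis: some participants will have no usable prior mammogram, and some specimens may not be the whole imaged breast. The number of usable pairs should be reported with the result.
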